## Background

1.

Autism spectrum disorder (ASD) is a prevalent childhood neurodevelopmental disorder that affects approximately 0.97% of the population (1). The rising incidence rates have been attributed differently from one country to another to different factors such as increased awareness and greater societal recognition of ASD (2), changes in diagnostic tools and criteria, lowered stigma, and improved health service organization (3).

Although ASD is a very heterogeneous disorder with many associated psychiatric and medical co-occurring conditions, specific core symptoms define its diagnosis. This disorder is largely defined by impaired socio-emotional reciprocity and limited interpersonal communication, a diagnostic criterion in the DSM 5 [Diagnostic Statistical Manual of mental disorders (4)].

The construct of social skills is both multidimensional and highly related to many other important constructs: pragmatic language, cognition, and mental health (5, 6).

Several definitions of social skills agree that these skills are learned behaviors that enable individuals to communicate and interact competently and appropriately with each other, both verbally and non-verbally, in a given social context. This wide group of abilities emerges from the appropriate execution of social cognition processing that allows us to predict and understand other people’s intentions, feelings, emotions, and behaviors (7). They are essential for establishing and maintaining harmonious social relationships as well as for social and professional integration.

People with ASDs have difficulties in acquiring and mastering these competencies. According to clinical studies and descriptions, these difficulties emerge early in a child’s development (poor eye contact, lack of joint attention, lack of anticipatory response, delay in the development of language, receptive language, and symbolic play …) (5, 8, 9). Wing et al. identified three groups of children with ASD: those who were aloof and socially remote, those who moved away from social overtures but could be engaged (passive interaction), and those who engaged in interactions in unusual or odd ways (odd interaction) (10).

Social communication deficits present in ASD are wide-ranging and individuals vary broadly in their clinical presentation. Consequently, impaired social learning in early childhood, differences in the maturation of social behavior continue through developmental cascades (11). Indeed, adolescents with autism frequently struggle with discomfort or ineptitude in social interactions. Their social skills deficits are characterized by pedantic or odd speech patterns, lack of empathy, lack of social problem-solving ability (12), difficulties interpreting body language (13), poor social–emotional reciprocity and non-verbal communication skills impairments (14), difficulties in process facial expressions (15, 16) and impairments in identifying others’ thoughts (17). These difficulties, particularly in adolescence, are the source of traumatic experiences of rejection and misunderstanding in school and social environments. Outside of relational outcomes, Frith (18) further proposed that the social deficits may impact also academic performance and employment outcomes. They are also correlated with a high rate of self-blame and low self-esteem in adolescents with ASD (19). It is no wonder that young persons with ASD are considered particularly vulnerable to developing depressive and anxiety symptoms (20, 21).

In the past decade, there has been significant attention to developing and disseminating information regarding social skills interventions and social skills training that demonstrated mixed outcomes in ASD. In fact, social skills training (SST) which is inspired from cognitive and behavioral interventions and social learning theories (22), is recommended by the French National Authority for Health (Haute Autorité de Santé, or HAS) in ASDs (23). However, fewer studies have included adolescents with ASD. A review of 10 SST intervention studies for youth with ASD, in 2008, showed that seven (70%) of the studies have a positive treatment effect on social skills and significant gains on real-life problem-solving tests (24). In a 2013 Cochrane review evaluating the effects of social skills groups for individuals aged 6–21 with ASD, Reichow et al. (25) showed that there is an improvement in social communication in these groups, friendship quality, and a decrease in feelings of loneliness.

In addition to genetic and neurobiological factors, social dysfunction patterns in ASD are suggested to be primarily underpinned by impairments in cognitive function (26, 27). In our understanding of the underlying cognitive deficit exhibited by people with ASD, psychological theories have been a topic of much debate. They argued that this impairment includes a deficit in theory of mind (ToM) (28, 29), dysexecutive syndrome (30, 31), and a weak central coherence (32). That could explain why aspects of social and communicative behavior that require social insight are impaired in autism. In fact, the adaptation to the immediate social environment requires several high-level cognitive processes that allow the individual to regulate his behavior by taking into account the behavior of others. According to Mottron (33), the social deficits in autism would be explained by the deficit of some basic cognitive functions. These functions are often convoluted and operate synergistically. The notion of weak ‘central coherence’ (CC) in autism has been postulated by 32. It describes a cognitive style rather than deficit (34). In their interaction with their environment, individuals on the autism spectrum disorder tend to excel at focusing on extreme detail and fail to extract global form and meaning. It may be related to ToM because in order to understand the thoughts and emotions of others in a real-life situation, an individual needs to be able to take into account the social context and integrate diverse information from a variety of sources (34).

ToM is one of the most relevant concepts in the field of social cognition, particularly in the case of autism (29). It is defined as the ability to ascribe mental states to oneself and others and to interpret the behavior of others in terms of mental states. It makes it possible to identify the emotion, desires, and thoughts, to understand the communicative intentions of others, and to understand infraverbal communication. It underlies also empathy skills (35). Possessing a functional theory of mind is considered crucial for success in everyday human social interactions. Empirical findings confirm this deficit in mind-reading in ASD based on inferior performance on assessment tasks (mindblindness) (36). A poor ToM will significantly compromise their socially mediated learning.

ToM and the pragmatic dimension of language are also closely intertwined. Several findings from different approaches (mainly neurological and developmental studies) support this perspective (37–39). According to Dardier (40), the pragmatic of language is the “interface between cognitive, social and linguistic developments.”

The major proponents of the concept of “executive function” (EF) have been Russell et al. (41), who argue that basic executive processes underlie the infant’s discovery of his/her own agency. Impairments in ‘Executive Function’ are broadly cited in ASD and have been posited to underlie the core difficulties both in the social and non-social domains. They are essential to guide behavior in a continuously changing environment (42). The theory of dysexecutive syndrome in autism comprises defects in working memory, response inhibition, initiation and monitoring of action, cognitive flexibility, and impulse control (43, 44). Minshew and Goldstein (45) found that individuals with ASD were more impaired than those without autism when the complexity of exercises was increased. These difficulties may clarify some behavior problems such as cognitive rigidity, perseveration to routines, failure in adjusting behavior to changing environmental demands, and stereotypies observed in ASD (46). It is obvious that the executive dysfunction account addresses the social and communicative aspects and non-social aspects of autism.

From this perspective, cognitive deficits are not solely a manifestation of neuropsychological dysfunction, but rather social-cognitive dysfunction (47).

Cognitive remediation (CR), based on the theory of brain plasticity, is now considered a crucial therapeutic approach in the management of cognitive dysfunction. A narrow range of researchers studying the use of CR in ASD has shown improvements in social cognition (48, 49) or executive function (50, 51). A cross-sectional study, by Hajri et al. (52), investigating improvements in executive and academic functioning in 25 patients with ASD after the use of a cognitive remediation program (Cognitive Remediation Therapy), showed a significant improvement in intellectual efficiency, working memory, cognitive flexibility, planning and academic performance.

Currently, there is a wide range of challenges, and paths for fundamental advances in ASD therapeutics that have reported that this population do not readily generalize and maintain skills. Successful generalization in necessary for an intervention to have benefits in everyday life beyond the original learning environment. CR and SST show only moderate effects and transfer into reals world is insufficient. Thus, a combination of CR and skills groups could help.

In view of all these data, we propose to conduct a study aimed at improving the maintenance and generalization of skills to new situations and environments in this population, by adapting the NEAR method. The main objective is to evaluate the effect of cognitive training combined with the NEAR approach (CT-NEAR), delivered in a social rehabilitation framework, on the global functioning of adolescents with autism. The goal is to reduce the negative impact of impaired cognition on the daily life and to enhance of the global functioning.

NEAR, which is used with a variety of cognitively challenged psychiatric populations, includes computer based cognitive exercises and verbal “Bridging groups” to help patients transfer their practice of cognitive and social skills with real-world situations. Adolescents with ASD require more of a focus on social cognitive skills which is typically provided in the NEAR program. Our adaptation work aims to provide, through these skill-building groups, an opportunity to improve social skills as well as other competencies. Thus, the adaptations would increase focus on improving language pragmatics, ToM, empathy, and attributional style. These adapted “Bridging groups” would also aim to increase the effectiveness of the therapeutic process by encouraging the process of generalization that promotes the application of cognitive skills and compensatory strategies acquired in the sessions to situations outside of the group (53).

## Methods

2.

### Interventions

2.1.

#### Method of choice: neuropsychological educational approach to remediation (NEAR)

2.1.1.

This holistic approach to cognitive remediation, developed and disseminated by Medalia and colleagues, was specifically designed for use with psychiatric patients (47, 53). NEAR aims to improve cognitive functions that have been identified as sufficiently impaired to hamper functional outcome. This method combines computerized cognitive exercises and bridging groups inspired from cognitive behavioral therapy. It promotes a smooth interplay of cognitive and social–emotional variables in everyday functioning. NEAR has a specific focus on motivation which has benefits on learning and is also associated with increased levels of autonomy, self-esteem, and positive experiences (54). This determinant is very important for young patients. Further, this rehabilitation program promotes awareness about learning style, learning strengths, and weaknesses so participants gain a sense of competence and confidence in their ability to acquire skills (47).

The NEAR model was designed to be easily implemented in a variety of settings and cultures, which has facilitated worldwide dissemination and the translation of materials into multiple languages. In France, there has been a large-scale adoption of the NEAR program, and clinician training and patient materials have been translated into French, which provides a ready source of materials for use with the French speaking Tunisian population. As implemented throughout France (55), participants are seen in groups of 4–8, with each having their own computer to work on. The duration of a clinician led session lasts 90 min, with 45 min reserved for computerized exercises and 45 min for the bridging group. The role of the clinician in NEAR sessions varies from instructing to assessing, to observing, to facilitating a positive learning experience by encouraging participants to seek and find strategies. Manuals of bridging group discussions are available to enable clinicians to relate activities of daily life to the cognitive skills worked during the sessions. Worksheets and a variety of forms are provided in the clinician manual (53).

The computer-based exercises to be performed during each session are personalized to each participant’s cognitive needs, as identified by a neurocognitive evaluation and interview. Thus, participants are seen in a group but work on different exercises personalized to their needs. These exercises may target several cognitive domains such as visual and auditory attention, focused and divided attention, sustained attention, processing speed, verbal and visual working and long-term memory, planning, problem-solving, inhibition, and mental flexibility. The repetition of the exercises and the presentation of the results and the level of progress on the screen of each participant enable the reinforcement of autonomy and favor the use of errorless learning. Participants conclude their computer based cognitive activities for the day by completing a worksheet about the exercises completed, the level reached, the cognitive function worked on, the link with daily life. Further comments may pertain to the strategy used in each exercise, the benefit(s) of the session, and the difficulties encountered. These activities encourage self-reflection, metacognition and enhanced cognitive skillfulness to handle everyday situations.

The Bridging session manual used in France covers 34 sessions organized in 8 modules (Table 1).

**Table 1 tab1:** The NEAR France program modules.

	Title	Number of sessions
Module 1	Introduction to cognitive skills	7
Module 2	Verbal reasoning and problem solving	3
Module 3	Thinking about your own thoughts	5
Module 4	Planning and organization	4
Module 5	Attention	4
Module 6	Effective communication	8
Module 7	Healthy living	2
Module 8	Conclusion	1

#### Adaptation of NEAR method to adolescents with ASD

2.1.2.

In our study, the 6th Module (Effective Communication) will be enriched and amended by adding other tasks aiming to improve the development of non-verbal communication, conversational skills, assertiveness, social skills in group situations, and emotional recognition. We will also add a new session entitled “Social rules and respect for others” (two parts). This module will then include 8 sessions. The sessions of this module are structured around a first theoretical part. The second part consists of an application in the ecological environment (practical exercises carried out in small groups). The approach through the different sessions is progressive, allowing to reach the most complex objectives related to social autonomy.

According to the theme of the session, the moderator will choose 3 or even 4 of the following functions per session: Verbal and non-verbal theory of mind/ Facial emotion recognition /Empathy/ Recognition of simple and complex emotions/ Recognition of automatic thoughts (reinforcement: this topic was addressed in module 3)/Attributional styles/ Pragmatics of language.

Topics will include problematic situations for adolescents with ASD: two-way conversation with a peer, teacher…; sharing information with peers; understanding humor, teasing, innuendo, and metaphors; communication through messaging and social networks; learning social rules; respect for others, recognizing one’s limits in an interaction; organizing meetings/outings with peers; management of friendships and romantic relationships; management of stress caused by school learning and bullying; handling disagreements and arguments.

Tools that will be used in this module are:

➢ Scenarios of problematic social situations in autism, taking into account cultural particularities (Theory of Mind). We created a list of social story ideas that include common social situations that autistic children might encounter to help them to cope with various changes and everyday life transitions. Those situations, allow them to have a better comprehension of their behavior as well as others’ and provide tools that aim to teach them how to make and maintain friendships, join group activities, initiate friendships and social relationships as well as maintain them. The use of these social narratives aims also to teach them how to ask for help and get unstuck.Role-playing exercises with peers in order to enhance participation in the community and support outcomes like self-esteem and friendships. Role-plays are preceded by the direct instruction of skill so that adolescents have a foundation on which to then practice the skill.➢ Digital videos and photographs expressing the six basic emotions (happiness, anger, sadness, disgust, fear, and surprise), presented by actors of different ages and genders, to improve the recognition and expression of facial emotions. The items are coded according to Ekman’s “Facial Action Coding System” method. During this task, each facial expression with the respective proposals remains on the screen for 15 s. After this time and when the participant has not been able to select his choice, the correct answer will be displayed on the screen. Once an answer is selected for a given face, the response time will be recorded and the correct answer will be displayed on the screen.➢ Mime of emotions to improve emotional skills through facial expression recognition. During this task, the participant takes it in turns to take a card and mime the emotion while the others try to guess. Then, each candidate talks about an event for which he experienced this emotion.➢ “Feelings” Game: a board game created in 2015 by Jean-Louis Roubira and Vincent Bidault (56). This game aims at expression and empathic exchange through emotions. “Feelings allows you to learn more about yourself and the other players, to be open to all the ways in which we are different or the same, and to consider everyone as a unique person,” Thibaut Quintens (Act in games). Around the Emotions Track placed in the middle of the table and after reading a given situation (120 Situation cards divided into 3 themes, family, friends, and school), each player is invited to position himself on one of the proposed emotions (24 Emotions cards) and which he feels closest to. Then, persons exchange glances with their playing partner and place a bet on the emotion they think their partner has chosen (72 Vote cards, of different colors, 9 per player). Each player selects from his Vote cards the one he thinks corresponds to the personal emotion of his partner. Each player selects from his Vote cards the one he thinks corresponds to the personal emotion of his partner. Each player guesses the feeling chosen by their teammate. When both players guess the right feeling, they earn three points. If just one of them guesses the right feeling, they earn one point, and if neither of them guesses they have no point. The aim is to find the emotions of the other person, the track of emotions will then reflect the degree of empathy and openness to others. ‘Feelings’ can be used as a trigger to discuss feelings in specific situations (56, 57).➢ Team Building Activities: group discussion based on free associations of ideas (using a dashboard), discussions around short videos (using a humorous Tunisian television series) to predict a character’s behavior based on his or her mental state, telling a story to their teammate.➢ Home tasks, at the end of each session, to promote generalization and spontaneity (transferring skills into natural environments and everyday interactions): introduce themselves and get leadership on making new friends, discuss their interests with others and suggest a group game, plan an outing with your friends.

### Study design

2.2.

Our study is a prospective, experimental, open, and non-randomized controlled trial.

This study research is carried out in the Child and Adolescent Psychiatry Department in Razi University Hospital-Manouba-Tunisia. It is conducted in collaboration with the C3RP team (Resource Center for Cognitive Remediation and Psychosocial Rehabilitation, Ile-de-France) -Sainte-Anne Hospital and under the supervision of [name] (Ph.D. – Professor of Psychology at Columbia University Irving Medical Center and Director of Cognitive Health Services for the New York State Office of Mental Health, United States).

### Participants and screening

2.3.

The inclusion criteria are:

ο Adolescents aged than 13 years, meeting the Diagnostic and Statistical Manual for Mental Disorders (DSM-5) (4) criteria for ASD confirmed by the ADI-R [Autism Diagnostic Interview-Revised, (58)] criteria, without mental retardation, followed in the Child and Adolescent Psychiatry Department (out-patient clinic) in Razi University Hospital-Manouba-Tunisia. Patients who agreed to participate in our study were retained.ο Sufficient level of understanding and communication in Arabic and French (allowing them to understand the instructions during the care sessions).ο Regular school curriculum.

It should be noted that adolescents treated with psychotropics will be included, with the condition that there will be no change to the drug treatment (molecule, dosage) during the period of study.

A certified therapist will conduct a standardized interview for the clinical and diagnostic evaluation of these adolescents (using the ADI-R).

Parents obtained information concerning the study and had the opportunity to ask questions before agreeing to the participation of their children, and during the study.

The non-inclusion criteria are:

ο Out-of-school patientsο Mental retardation or severe cognitive impairmentsο A history of neurological disorderο Severe behavioral disordersο Electroconvulsive therapy in the past 6 months

Exclusion criteria are:

ο Non-achievement of the programο Missing more than three sessionsο Non-achievement of assessments after finishing the therapy

Strategies to improve adherence to intervention:

ο Method of choice: NEAR program enhances intrinsic and extrinsic motivation by employing more engaging and interesting exercises packages for cognitive practice, involving participants in choosing the focus of training.ο All candidates received two psycho-education sessions: one individual and one group session in order to raise their awareness, motivation and to present the program (number of sessions, progress, interest…).ο Parent involvement in the program and home tasks.

Our study will include 30 patients that will be divided into two groups: NEAR group/ control group (a group that will assign usual care).

This allocation of patients between the two groups would be made according to the following criteria:

ο Teenage motivationο Their availability and parent’s one to accompany them to their clinical evaluations and therapeutic sessions.

The patients included in the NEAR group will be divided into three groups of five patients each. The rhythm for sessions for each group is one to two sessions per week. The duration of the program will be about 6 months.

In our study, the duration of the sessions will vary according to the capacities of the participants and the exchanges between them (about 90–120 min).

Two pre-trained therapists lead the sessions and are assigned to follow the progress of each participant.

All selected patients will have an assessment of global functioning, cognitive function (social cognition and neurocognition) pragmatic skills, social skills and self-esteem, and at baseline (T1), 1 week after the end of the NEAR program (T2), and 6 months later (T3). The same interval will be kept for three sessions of evaluations of the control group.

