## Statistical analysis

3.

Data collection and statistical analysis will be performed using the Statistical Package for Social Sciences (SPSS) version 25.

We will proceed to the comparison of the different scores of each group at the beginning and at the end of the study as well as to the comparison of the progression of the two groups between them at the beginning and at the end of the study.

The primary objective of our study is to facilitate the transfer of new skills to daily life and thus the global functioning of this population. Primary outcomes will be based on the GAF score and The Global Executive Composite score of the BRIEF. All other measures (social cognition, neurocognition, social skills, pragmatic skills and self-esteem) will be secondary outcomes and will be assessed descriptively.

For the descriptive statistics, we will calculate means and standard deviations for age and educational level and for categorical data, e.g., sex we will use Fisher’s Exact Chi-squared test.

For each neurocognitive and social cognition domain measure, we will conduct *t*-tests for independent samples to examine baseline differences for this sample. To examine Group X Time interaction for measuring treatment effects, we will conduct a Repeated Measure-Analysis of Variance (RM-ANOVA) that compared the difference scores of NEAR-group vs. Control-group at baseline and at the completion of the intervention.

A RM-ANOVA will also be used to examine differences in pragmatic skills, social skills and self-esteem.

For the two measures where there were statistically significant baseline differences, we will repeat the RM-ANOVA using baseline cognitive scores as a co-variate to control for baseline differences.

The significance level for all statistical analyses will be set to *p* = <0.05.

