## Discussion

5.

The NEAR program is tailored to the participant’s age and interests. It will address the adolescent’s behavior, cognitive and communication skills and offer regular reinforcement of positive actions. Also, parents as well as other family members, will be involved in the treatment program (through home tasks) so that it becomes part of the adolescent’s daily life.

At the end of our study, we expect to see an improvement in terms of social functioning and social skills in this population and so a better social integration and quality of life. Thus, this adaptative program could be a promising socio-cognitive intervention that creates new perspective for adolescents with ASD. In fact, the social demands of adolescence present a particularly difficult developmental stage and a continuous challenge throughout the life span, particularly for people with ASD. Despite their social impairments, maintaining and sustaining friendships remained the greatest challenge for adolescents with ASD and they often express concerns about their lack of reciprocal friendships (80).

Also, we expect neuropsychological improvements, mainly in theory of mind (ToM), which is one of the most frequent and disabling cognitive impairment in autism (28, 81). This improvement could be helped by the enrichment added in bridging groups with scenarios of problematic social situations in autism. This will promote the development of social coping skills, as well as to work through behavior management strategies. In fact, social stories can be effective for individuals with ASD and provide a framework for understanding and addressing ToM deficits characteristic of these individuals (82–84). The choice of group role-plays is motivated by the results of many studies that discuss the use of this method to develop social and pragmatic skills of autistic children (85, 86). Furthermore, “Feelings” game will be used to enhance empathy in our population. It uses two game mechanics to generate empathy: naming which emotion is felt in a particular situation (Introspection) and guessing which feeling other people feel in the same situation (decentering) (56). It is important to highlight that people with autism have a deficit of cognitive empathy but a surfeit of emotional empathy (87).

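### Age is described but enters no stated model, so in this non-randomised comparison age-related change could fall into the Group x Time term if the arms differ systematically in age

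*Protocol article*

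**What the plan says.** All points are from the protocol article.

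- **Design (Study design).** The trial is a "prospective, experimental, open, and non-randomized controlled trial".
- **Allocation (Participants and screening).** The section says "This allocation of patients between the two groups would be made according to the following criteria", and lists the adolescent's motivation and the availability of adolescent and parent for evaluations and sessions. No matching or stratification on age is stated.
- **Age at entry (same section).** The criterion is printed as "Adolescents aged than 13 years", with no comparator and no numeric upper limit. Other criteria bound age indirectly: patients are "followed in the Child and Adolescent Psychiatry Department (out-patient clinic"), and they must follow a "Regular school curriculum".
- **Age in the analysis (Statistical analysis).** Age is summarised only: "we will calculate means and standard deviations for age and educational level".
- **Treatment effect (same section).** It is the Group x Time interaction of a repeated-measures ANOVA from baseline to completion of the intervention.
- **Covariates (same section).** For two measures with significant baseline differences, the model is repeated "using baseline cognitive scores as a co-variate to control for baseline differences". No other covariate is named. The primary outcomes are GAF and the BRIEF Global Executive Composite.

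**The concern.** Randomisation would make an age imbalance a matter of chance, which the nominal 5% level already allows for. Here nothing in the stated allocation does that. Whether a parent can accompany the adolescent, and how motivated the adolescent is, could both vary with age. The article does not say so, and the direction cannot be predicted.

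The outcome is change over about 6 months of adolescence. If younger and older participants change at different rates, and one arm is systematically older, the difference in maturation lies inside the Group x Time term and cannot be told apart from a NEAR effect. The stated covariate rule does not help: it concerns baseline cognitive scores on two measures and brings no age term into any model, including those for the two primary outcomes.

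**Working it through.** The article gives no power calculation, effect size or SD, so there is no figure of its own to reproduce. The check asks how large the bias could be.

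**Inputs from the article**
- Total N = 30. The NEAR arm is three groups of five, 3 x 5 = 15, so control = 30 − 15 = 15.
- Significance level 0.05 (taken as two-sided, since sidedness is not stated).
- The model covers T1 to T2, about 6 months.

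**Inputs assumed, because the article gives none**
- D, the age gap between arms in SD of age: 0.5 or 0.8.
- r, the within-arm correlation of age with change: 0 to 0.5.

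**Method.** With two time points, the Group x Time test is equivalent to a two-sample t-test on change scores, here with 28 degrees of freedom (critical value 2.048). With no NEAR effect and the within-arm SD of change set to 1:
- bias = r x D
- noncentrality = r x D x √(15/2) = 2.739 x r x D
- the false-positive rate is the two-sided tail area of the noncentral t.

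| D | r | Bias (SD of change) | Noncentrality | False-positive rate |
|---|---|---|---|---|
| 0.5 | 0 | 0 | 0 | 5.0% |
| 0.5 | 0.1 | 0.05 | 0.137 | 5.2% |
| 0.5 | 0.3 | 0.15 | 0.411 | 6.8% |
| 0.5 | 0.5 | 0.25 | 0.685 | 10.1% |
| 0.8 | 0 | 0 | 0 | 5.0% |
| 0.8 | 0.1 | 0.08 | 0.219 | 5.5% |
| 0.8 | 0.3 | 0.24 | 0.657 | 9.7% |
| 0.8 | 0.5 | 0.40 | 1.095 | 18.5% |

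These rates are conditional on a gap of size D. They describe a systematic imbalance, not the average over random allocations.

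**What adjustment does to precision.** Adding age multiplies the residual variance by 1 − r². Because age is then correlated with arm, the variance of the group effect is also multiplied by 1 + 7.5D²/28:
- D = 0.5: 1 + 7.5 x 0.25/28 = 1.067
- D = 0.8: 1 + 7.5 x 0.64/28 = 1.171

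Net factor on the variance of the treatment estimate (ignoring the one lost degree of freedom):

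| r | D = 0.5 | D = 0.8 |
|---|---|---|
| 0 | 1.00 x 1.067 = 1.07 | 1.00 x 1.171 = 1.17 |
| 0.3 | 0.91 x 1.067 = 0.97 | 0.91 x 1.171 = 1.07 |
| 0.5 | 0.75 x 1.067 = 0.80 | 0.75 x 1.171 = 0.88 |

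The effect on precision therefore runs from a 20% fall in variance to a 17% rise. The rise of 17% is a standard error about 8% larger (√1.171 = 1.082).

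**The case against.** **A stable age difference cancels.** Group x Time compares change, so if older adolescents merely score higher or lower throughout, nothing is biased. This stands. A reader might infer that any age difference between the arms will be read as a NEAR effect. The documents do not support that: age must also predict change between T1 and T2.

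**The article does not show that it does.** The Discussion says that "the social demands of adolescence present a particularly difficult developmental stage", but this does not say that younger and older adolescents progress at different rates. The link between availability and age is likewise conjecture. This also stands, and is why the range above starts at r = 0, where there is no harm.

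**Chance imbalance is no argument.** At 15 per arm, random allocation would give an age gap of at least 0.5 SD in 17% of trials (standard error √(2/15) = 0.365). The nominal 5% already includes this. Only a systematic gap inflates the error rate, and its size is unknown.

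**Age is not unbounded.** A reader might take the garbled criterion to mean an open age range, and see that as the cause of the problem. The word adolescents, the clinic and the schooling requirement all limit age, though not numerically. The missing word looks like a clerical slip, and it does not cause confounding; the allocation does.

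**Covariates may be listed elsewhere, and motivation matters more.** A statistical analysis plan that is not shown could add covariates. But the article does state a covariate rule, and age is not in it. It is also true that adjusting for age leaves confounding by motivation untouched. That limits what the change achieves without removing the reason for it.

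**Conclusion.** The point holds in a conditional form. Allocation is non-random, nothing stated balances age, and age is recorded and summarised but enters no stated model. Bias follows only if two conditions both hold: a systematic age gap between arms, and a relation between age and change over about 6 months. The documents establish neither and exclude neither.

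Under the assumed correlations of 0 to 0.5, the consequence runs from none to a false-positive rate of 10% at a 0.5 SD gap, or about 18% at 0.8 SD. The upper figures need a strong relation; at a correlation of 0.1 the rate stays between 5.2% and 5.5%. The case for adjustment is protection against bias. A reader might also expect a smaller standard error in every case, but the working shows that it can go either way.

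This is a modest and inexpensive improvement to the stated model, and not a remedy for the allocation method. The wording of the age criterion is a separate editorial correction.

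**What to change.** 1. Pre-specify age at T1 as a covariate for GAF and the BRIEF Global Executive Composite. Either include age with its interaction with time in the repeated-measures model, or model the T2 score on arm, T1 score and age. In the repeated-measures form an age main effect alone would not do, because it does not adjust the Group x Time contrast.
2. Do the same for secondary scores that are not age-normed, wherever they are compared between arms.
3. Fix this in advance, and apply it whether or not the arms differ significantly in age. With 15 per arm, a non-significant test is weak evidence of balance.
4. Say in the report that age adjustment does not deal with confounding by motivation.
5. Separately, correct the eligibility line to give the age limits actually applied.

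The cost is one degree of freedom out of 28, with no new data, since age is already recorded. The interval may be somewhat wider if the arms differ in age but age predicts change only weakly.
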